**LIST OF ABBREVIATIONS AND RELEVANT DEFINITIONS**

|                |                                                                                                                                                                                                                                                                                                                                                  |
|----------------|--------------------------------------------------------------------------------------------------------------------------------------------------------------------------------------------------------------------------------------------------------------------------------------------------------------------------------------------------|
| ABR     | ABR form, General Assessment and Registration form. This is the application form that is required for submission to the accredited Ethics Committee (In Dutch, ABR = Algemene Beoordeling en Registratie)                                                                                                                                 |
| AE      | Adverse Event                                                                                                                                                                                                                                                                                                                             |
| AR      | Adverse Reaction                                                                                                                                                                                                                                                                                                                          |
| CA      | Competent Authority                                                                                                                                                                                                                                                                                                                       |
| CCMO    | Central Committee on Research Involving Human Subjects; in Dutch: Centrale Commissie Mensgebonden Onderzoek                                                                                                                                                                                                                               |
| CV      | Curriculum Vitae                                                                                                                                                                                                                                                                                                                          |
| EU      | European Union                                                                                                                                                                                                                                                                                                                            |
| GCP     | Good Clinical Practice                                                                                                                                                                                                                                                                                                                    |
| IB      | Investigator's Brochure                                                                                                                                                                                                                                                                                                                   |
| IC      | Informed Consent                                                                                                                                                                                                                                                                                                                          |
| METC    | Medical research ethics committee (MREC); in Dutch: medisch ethische toetsing commissie (METC)                                                                                                                                                                                                                                            |
| SAE     | Serious Adverse Event                                                                                                                                                                                                                                                                                                                     |
| Sponsor | The sponsor is the party that commissions the organisation or performance of the research, for example a pharmaceutical company, academic hospital, scientific organisation or investigator. A party that provides funding for a study but does not commission it is not regarded as the sponsor, but referred to as a subsidising party. |
| Wbp     | Personal Data Protection Act (in Dutch: Wet Bescherming Persoonsgegevens)                                                                                                                                                                                                                                                                 |
| WMO     | Medical Research Involving Human Subjects Act (in Dutch: Wet Medisch-wetenschappelijk Onderzoek met Mensen)                                                                                                                                                                                                                               |
| LLA     | [name].                                                                                                                                                                                                                                                                                                                  |
| VNP     | Nurse practitioner specialised in vascular surgery (in Dutch: verpleegkundig specialist vaat)                                                                                                                                                                                                                                             |
| CM      | Mw [name] MD                                                                                                                                                                                                                                                                                                                          |
| EVAR    | EndoVascular Aneurysm Repair                                                                                                                                                                                                                                                                                                              |
| MMSE    | Minimal mental state exam                                                                                                                                                                                                                                                                                                                 |
| MNA     | Minimal nutritional assessment test                                                                                                                                                                                                                                                                                                       |
| WHOQOL  | World health organisation Quality of Life,                                                                                                                                                                                                                                                                                                |

## Optimalisatie oUderen Traject pre –Operatief (OUTO)

**SUMMARY**

**Rationale:** Due to a growing elderly population, the demand for health care is expected to increase. Elderly are prone to have a higher incidence of delirium, which results in a longer hospital stay, more complications, and a higher rate of mortality.

**Objective:** Our aim is to reduce the incidence of delirium in patients over 70 from 15% to 7.5 %. Our secondary aim is to reduce length of hospital stay, number of complications and mortality.

**Study design:** This study is an observational interventional study.

**Study population:** All men and women aged 70 or older who will undergo elective surgery, for either colorectal cancer or abdominal aortic aneurysm are included in this study. Both laparoscopic (including EVAR) and open procedure are investigated.

**Intervention (if applicable):** Within one week after confirming the indication for surgery and five weeks before surgery patients will visit the 70 PLUS outpatient clinic in our surgery department. We aim to investigate all factors related to frailty. A dietician and a physiotherapist will provide instructions to apply at home. If anaemic, an intravenous iron injection will be given. A geriatrician will be consulted if the patient has a high chance of developing a delirium during admission.

**Main study parameters/endpoints:**

Incidence of delirium is our primary outcome. Secondary outcomes include duration of hospital stay and six month mortality. We will investigate aspects of frailty that are related to the incidence of delirium.

**Nature and extent of the burden and risks associated with participation, benefit and group relatedness:**

Patients will be asked to answer questionnaires at the outpatient clinic, during admission, and at 6 and 12 months after surgery. At the outpatient clinic blood will be drawn, which is repeated at admission and on the day of discharge. Also physiotherapists will examine the physical condition. A personalised exercise program will be made for each patient. These exercises must be done daily and a diary must be kept.

## 1. INTRODUCTION AND RATIONALE

The population of people above 65 years old is expected to double in the next 35 years. The increase of age is associated with an increase in need for medical care and number of patients requiring surgery. A higher rate of post-operative complications, like a delirium (37%), longer hospital stay, ICU admission, and mortality is associated with increasing age.[1, 2]

In our hospital, within the population of 70 years or older, approximately 85 patients per year undergo surgery for colorectal cancer and about 50 patients per year undergo surgery for abdominal aortic aneurysm. We expect an increase in the number these surgical procedures performed during the coming years (also due to the implementation of screening programs).

A delirium is often a fatal disorder. It affects as much as 50 % of the elderly people who are hospitalised. In the population described above, the incidence of a delirium is about 15%. The 6-month mortality is increased within patients with a postoperative delirium (20%) versus no delirium (3%). [3] In short a delirium is a common complication after surgical intervention and results in a significant decrease in quality of life, an increased rate of complications, mortality and additionally is associated with high costs. Therefore a delirium holds essential health relevance.

The cause of a delirium can be the result of a single factor but is mostly a combination of different factors at once. Many factors have been identified and validated to be an independent cause of a delirium. These factors of frailty are for example the patient's nutritional state, physical health, the use of medication, the patient's mental state, laboratory results (such as anaemia and renal function), delirium in patient's history, visual and hearing impairment.

At the moment physicians are already more aware of these frail elderly and these factors of frailty but it is only tackled at admission in hospital or at long care facilities. A delirium is preventable in 30 to 40 % of the cases. Therefore the Hospital Elder Life Program (HELP), a worldwide non –pharmaceutical program, is implemented. This program starts at admission and is proven to be effective to prevent a delirium. [3-5] Another recent study, for patients with an acute hip surgery, shows that specific ortho – geriatric care during admission improves the outcome 4 months after surgery. [6]

We believe that these elements of frailty can be approached and tackled before admission in case of elective planned surgery. So improvement of patient's nutritional state, patient's physical health or deviant laboratory results can be achieved.

The goal of this study is to anticipate on these factors of frailty in an early phase of care to decrease the incidence of a delirium. We will optimise patients during 5 weeks before their surgery, with the intention to minimise the incidence of delirium, complications, hospital stay and mortality. Both a non–pharmaceutical as a pharmaceutical approach is implemented in this program.

## 2. OBJECTIVES

Our primary aim is to address and tackle the factors of frailty in an early phase, which is possible in elective planned surgery.

We hypothesise that *optimal* preparation, starting 5 weeks before surgery, will reduce the incidence of delirium from 15% to 7,5%. [7]

Our secondary aim is to reduce post-operative complications, hospital stay, and the 6 months mortality compared to a retrospective database made.

We will analyse all pre-, peri -and postoperative factors and the effect on the incidence of delirium, other complications and mortality. This will be done to create a risk model for patients to assess the risk for adverse events post-operatively. Also the costs and cost-effectiveness of this program will be investigated.

In addition we will observe the experience of the first caregiver during the course of illness of the patient. More often direct family and friends are asked to help in the support of patients in need in all forms of care in the Netherlands. First caregivers are asked to actively support the patient in this program. Caregivers are often direct family, partner or children of who their social life and daily activities can be disturbed due to this program.

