### 3. STUDY DESIGN

This study will be a prospective interventional study, starting 1 January 2016, and planned until 31 December 2017.

A pre-operative clinical pathway is set up for patients of seventy years or older with surgical indication for colorectal cancer or abdominal aortic aneurysm, the 70 PLUS outpatient clinic in our surgery department. Within one week since indication for surgery is decided, a nurse practitioner, a physiotherapist and a dietician will see these patients and all factors of frailty will be investigated. If needed, a geriatrician will also see the patient for complete geriatric assessment and advice during admission to prevent delirium (criteria for CGA is described in *chapter 6.2 study procedures*). Diet advice and physical exercises will be given to all patients in need. Patients must follow these advices and keep a diary.

All patients aged  $\geq 70$  years will be included in this study to follow our pre-operative clinical pathway for optimisation. Also patients, who are not clinically fit to wait for 5 weeks will be included and optimised until surgery.

We propose an optimum preparation time during 5 to 6 weeks till surgery. This is based on the SONCOS quality guidelines 2015 for colorectal cancer, in which a maximum delay of 6 weeks is proposed from pathology result until surgery (Addendum: SONCOS quality guidelines 2015 for colorectal cancer ).

Prospectively gathered data of all cases will be compared to a retrospective, historical, control group of comparable patients from 1 March 2013 till 1 March 2015.

These patients have not been evaluated for factors of frailty in advance. This is a cohort of patients of the age  $\geq 70$  years who received treatment for colorectal cancer with or without neo-adjuvant therapy (radiation or chemotherapy). Both open and laparoscopic surgery will be included.

Also patient who received treatment for abdominal aneurysm of the age  $\geq 70$  are included. These patients underwent an EVAR or open repair. (Complete description of the pathway in the retrospective group is described in *chapter 6.2 Study procedure* and addendum *Amphia protocol Colonchirurgie*)

Only electively planned surgery is included, all emergent or urgent surgical procedures are excluded.

Data of patients in both groups will be gathered in the Amphia Hospital Breda, the Netherlands.

All information will be gathered using Hyperspace Version IU4 (Epic, Inc., Verona, WI).

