The historical patient group is based on patients admitted to the Amphia Hospital Breda in 2013 till November 2015. All data is gathered retrospectively but due to the use of the electronic patient file (Hyperspace Version IU4 (Epic, Inc., Verona, WI)) data was saved prospectively. No recent major changes have been made to indicate new procedures or pathways for the interventional care group compared to the historical patient group. The historical group will be comparable to the interventional care group in age ( $\geq 70$  years), ethnicity, gender and indication for surgery. Patients with emergent or urgent surgical intervention won't be included in this study, neither in the historical cohort. All patient who underwent neo adjuvant chemo – and / or radiotherapy are included.

However no questionnaires are undertaken in the historical group, hence the lack of prospective knowledge concerning dementia (scored by MMSE), quality of life or depression scale.

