## **6. METHODS**

### **6.1 Study parameters/endpoints**

#### **Main study parameter/endpoint**

Our main parameter is the incidence of a delirium is screened by DOS scores and confirmed by DSM IV classification. [10] Duration in days of the delirium will be investigated.

Our main endpoints are mortality within one year and follow up till 12 months after surgery.

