Data about the surgical procedure will be gathered. American Society of Anaesthesiologists' (ASA) classification for physical health is determined before surgery from history and physical examination by the attending anaesthesiologist. Anaesthesia time will be calculated as the duration between tracheal in- and extubation. Also blood loss during surgery and complications during surgery will be noted. All Patients undergoing surgery for colorectal carcinoma or abdominal aortic aneurysm surgery will receive general anaesthesia. Epidural anaesthesia is used as an adjunct as part of the fast track protocol. If patient is not eligible for epidural anaesthesia is not eligible (in case of allergies or coagulopathy), a Patient-Controlled Analgesia pump (PCA-Pump) with Morphine will be used as an alternative. Patients operated on with EVAR will not receive an epidural or a PCA. Other parameters gathered during admission, are complication, ICU stay, transfusion of packed cells, and mortality. Complications are classified using the Clavien –Dindo classification of surgical complications. [22]

At discharge (T3) patients will fill in WHOQOL-Bref, MMSE will be taken, the same blood will be drawn and the CSI will be filled in by first caregiver.

At follow up after six months (T4) and 12 months (T5) WHOQOL-Bref, CSI, MMSE and CESD-16 will be taken. Also function is tested using the TUG test and KATZ – ADL.

Table 2 describes when measurements are repeated to evaluate the effects of the intervention before surgery and after surgery. Laboratory results and physical exercises will be measured at admission.

Addendum describes all questionnaires, patient's chart, and laboratory results.

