### **6.6 Follow-up of subjects withdrawn from treatment**

Patients withdrawn from our study will follow usual follow up, only patient information about complications en mortality will be used.

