### 8.2 Secondary study parameter(s)

Secondary we will measure mortality within one year after surgery. Also duration of hospital stay, ICU admission, and complications during hospital stay will be investigated.

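### Mortality at 6 and 12 months is compared between a cohort with scheduled study contacts and a cohort known only from the hospital file, so control deaths after discharge may be captured less completely.

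*Protocol*

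**What the plan says.** **Mortality is compared between cohorts.** Section 2 gives the aim: "Our secondary aim is to reduce post-operative complications, hospital stay, and the 6 months mortality compared to a retrospective database made". Section 6.1 (main study parameter/endpoint) adds: "Our main endpoints are mortality within one year and follow up till 12 months after surgery". Section 8.2 lists the same outcome as secondary: "Secondary we will measure mortality within one year after surgery". Section 6.7 plans a check after one year that compares several outcomes, including 6-month mortality, with the historical group.

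**OUTO patients have scheduled contact after discharge.** Section 6.2 (OUTO Care) states: "At follow up after six months (T4) and 12 months (T5) WHOQOL-Bref, CSI, MMSE and CESD-16 will be taken". Function is tested at the same time points. For those who withdraw, section 6.6 states: "Patients withdrawn from our study will follow usual follow up, only patient information about complications en mortality will be used".

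**Controls come from existing records.** Section 3 says of the historical group: "All data is gathered retrospectively but due to the use of the electronic patient file", the entries themselves had been made prospectively. It also says: "However no questionnaires are undertaken in the historical group". One system is named for both groups: "All information will be gathered using Hyperspace Version IU4 (Epic, Inc., Verona, WI)".

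No death register, general-practitioner enquiry or other check of vital status is described for either cohort.

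**The concern.** The database is the same for both cohorts, but what prompts an entry in it differs. When an OUTO patient misses a planned 6- or 12-month appointment, staff have reason to ask why, and a death is likely to come to light. When a control died at home or elsewhere after discharge, no study procedure prompted that question. The hospital may have learned of the death through routine care, or it may not.

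If deaths are lost mainly in controls, observed control mortality falls below the truth and OUTO looks worse by comparison. Two things are at stake:

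- A real reduction in mortality could be hidden or could appear reversed.
- The mortality part of the one-year check in section 6.7 could suggest harm that is not there.

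This concerns where the data come from. The protocol itself fixes that source as the hospital file, so the point goes beyond analysis detail that could be left to a statistical analysis plan.

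**Working it through.** **The plan's own figure.** The only calculated figure is the delirium sample size: 15% vs 7.5%, 80% power, two-sided 5%, 275 per group. The unpooled formula is n = (1.960 + 0.842)² × (0.15×0.85 + 0.075×0.925) / 0.075² = 274.7, so 275 reproduces (the pooled formula gives 278). There is no calculation for mortality, and this one does not bear on the point.

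**Inputs for mortality.** Section 1 gives 6-month mortality of 20% with delirium and 3% without, and a delirium incidence of about 15%. Section 2 gives the target of 7.5%. The group size is 275.

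**Implied 6-month mortality**
- Controls: 0.15 × 20% + 0.85 × 3% = 5.55%, or 275 × 0.0555 = 15.3 deaths.
- OUTO, if delirium falls as planned and the same 20% and 3% apply: 0.075 × 20% + 0.925 × 3% = 4.275%, or 11.8 deaths.
- Difference: 1.275 percentage points, or 3.5 deaths per 275.

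**Effect of missed control deaths.** Let m be the share of control deaths not captured, with OUTO capture complete and uncaptured deaths counted as survivors. The observed control rate is 5.55% × (1 − m). The protocol gives no value for m, so the range below is an assumption.

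| m | Control deaths missed (of 15.3) | Observed ratio, equal true mortality: 1/(1 − m) | Chance that OUTO shows more deaths, equal true mortality | Observed difference (control − OUTO), implied benefit true |
|---|---|---|---|---|
| 0 | 0 | 1.00 | 46% | +1.28 points |
| 10% | 1.5 | 1.11 | 58% | +0.72 points |
| 20% | 3.1 | 1.25 | 69% | +0.16 points |
| 30% | 4.6 | 1.43 | 79% | −0.39 points |

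The chances are exact binomial, 275 vs 275.

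**Break-even.** The implied benefit disappears when 5.55% × (1 − m) = 4.275%. That gives m = 1 − 4.275/5.55 = 23%, or about 3.5 control deaths.

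**Power.** With complete capture, the power to detect 5.55% vs 4.275% at 275 per group is about 10%. A reader will therefore rely mostly on the direction and point estimate, which are what unequal capture shifts.

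**The case against.** **Nothing says that a control without a later entry counts as alive.** Section 8 says missing data are examined for patterns and multiply imputed, and a control whose status is recognised as unknown would fall under that rule. This stands against treating the ratios above as a prediction, since they require missed deaths to be scored as survivors. It does not remove the concern: a death that never reached the file may not be recognised as missing.

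**The OUTO side is not complete either.** The 6- and 12-month contacts are described as questionnaire and function visits, so finding deaths through them is an inference, though a reasonable one. Under section 6.4, patients who stop after surgery or discharge are noted as lost to follow-up and do not attend. Under section 6.6, withdrawn patients revert to usual follow-up. For them, capture resembles that in controls. This stands, and it narrows the asymmetry.

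**The control file may be good.** The protocol does not say how complete it is for deaths after discharge. Section 3 ends the control period in 2015 and section 6.3 expects analysis to finish in 2019, so later entries have years in which to settle many patients' status. This also stands: the 10-30% range has no anchor in the documents.

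**The comparison is secondary in section 8.2 and has little power.** With equal true mortality, the chance of a nominally significant result against OUTO (pooled z-test, two-sided 5%) rises from 2.5% with no loss to 4.7%, 8.5% and 14.6% at 10%, 20% and 30% loss. A false significant finding stays unlikely, but the estimate is still displaced.

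**Section 6.7.** A reader might infer that missed control deaths could by themselves end the study. The text does not support that. Its termination sentence refers to former research, the historical group is the comparator in the separate one-year check alongside other outcomes, and no numerical mortality limit is given.

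**Conclusion.** The concern holds as a risk of unequal capture. Six-month and one-year mortality is compared between a cohort with scheduled study contacts at those times and a cohort for which only the hospital file is named. No common method of establishing vital status is set. If deaths are missed mainly in controls, the bias runs against the programme and reaches the mortality part of the one-year check.

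A reader might go further and conclude that control mortality is understated, or that the status of every OUTO patient is actively established. The documents support neither statement. The size is unknown. The ratios of 1.11-1.43 rest on an assumed 10-30% loss in controls only, on missed deaths counted as survivors, and on equal true mortality of 5.55%. The firmer observation is how narrow the margin is: the benefit implied by the protocol's own figures is about 3.5 deaths per 275, so missing 23% of control deaths would cancel it.

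In-hospital deaths, in-hospital delirium and length of stay are not touched by this mechanism.

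**What to change.** In section 8.2, and for the mortality comparison in section 6.7, state that:

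- vital status at 6 and 12 months after surgery, with date of death where applicable, is taken for all patients in both cohorts, including withdrawn OUTO patients, from one common source such as a population register;
- absence of a death note in the hospital file is not taken as evidence that the patient is alive;
- patients with no register result are censored at last confirmed contact, or treated as missing under section 8, with the choice fixed in advance and the same in both cohorts;
- the number with unknown status at each time point is reported per cohort.

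The cost is one register query for about 550 patients, any permission it needs, and a few sentences of text. No extra patient contact is required.

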**Sample size calculation**

To reduce the percentage of delirium from 15% to 7,5%, with a power of 80% with 5% two-sided significance level, a 50 -50 trial, needs 550 patients, or 275 patient per study arm.

We propose to make a comparison to a retrospective control group of patients studied between 2012 and 2014 in the Amphia Hospital, Breda. [1]

We aim to include 275 patients in the prospective study, which is feasible during approximately 2 years of accrual.

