### 8.3 Other study parameters

All factors of frailty will be evaluated and analysis will be done to confirm association with the incidence of delirium.

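### The planned risk model sets no time limit on its predictors, so factors that follow delirium may be used to predict it, and delirium events are few for about 50 candidate variables

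*Protocol*

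**What the plan says.** Protocol Section 2 (Objectives) sets the scope of the factors: "We will analyse all pre-, peri -and postoperative factors and the effect on the incidence of delirium, other complications and mortality". It then gives the purpose: "This will be done to create a risk model for patients to assess the risk for adverse events post-operatively". It names no cohort, prediction time point or modelling method.

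Section 6.2 (OUTO care) lists what is collected: baseline characteristics, comorbidity scores, questionnaires, physiotherapy tests and laboratory results before surgery; operative data; and, during admission, pain scores, complications, ICU stay, transfusion and mortality.

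Section 8.3 adds: "All factors of frailty will be evaluated and analysis will be done to confirm association with the incidence of delirium".

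On the historical cohort, Section 3 says that frailty factors were not assessed in advance and adds: "However no questionnaires are undertaken in the historical group". The hypothesis in Section 2 is that preparation "will reduce the incidence of delirium from 15% to 7,5" per cent. The sample size section states: "We aim to include 275 patients in the prospective study".

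**The concern.** There are two problems.

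**Timing.** A model that assesses a patient's postoperative risk can use only what is known when the risk is assessed. Section 2 admits postoperative factors without restriction. Complications, ICU stay, transfusion and pain scores may occur after the onset of delirium, or because of it. Section 1 itself says that delirium leads to more complications. Complications are also both a candidate factor and an outcome in the same sentence of Section 2. A model built this way would appear to discriminate well partly because its predictors are consequences of the outcome, and it could not be applied before surgery.

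**Number of events.** A model that draws on all factors has far more candidates than the delirium events can support. Its apparent performance would be too good, and some frailty factors would be reported as confirmed by chance.

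At stake is the credibility of the risk model and of the frailty-factor findings. The comparison of delirium between cohorts is not at stake.

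**Working it through.** **1. The plan's own figure.** Inputs (Sample size calculation): 15% v 7.5%, "with a power of 80% with 5% two-sided significance level", 1:1. With the unpooled-variance formula, n per arm = (1.960 + 0.842)² × (0.15 × 0.85 + 0.075 × 0.925) / 0.075² = 274.7. This reproduces "needs 550 patients, or 275 patient per study arm". The cohort size used below is therefore sound.

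**2. Expected delirium events.**
- Prospective cohort at target: 275 × 0.075 = 20.6, about 21.
- Prospective cohort, no effect: 275 × 0.15 = 41.25, about 41.
- Both cohorts pooled, at target: 41.25 + 20.6 = 61.9, about 62. Questionnaire and physiotherapy measures would be missing in the historical half.

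**3. Candidate variables.** My count from Section 6.2, one term each: 17 baseline items (six of them comorbidities), 3 comorbidity scores, 2 questionnaires, 5 physiotherapy tests, 1 dependency score, 18 laboratory items and 2 nutrition scores. The sum is 17 + 3 + 2 + 5 + 1 + 18 + 2 = 48 at the first visit, before any operative or postoperative item. About 50 is therefore not an inflated count. As a much narrower comparison, the covariates named in Section 8 for the primary model come to 16 terms.

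**4. Events per candidate.**

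| Scenario | Events | 50 candidates | 16 terms |
|---|---|---|---|
| Prospective, target | 20.6 | 0.41 | 1.3 |
| Prospective, no effect | 41.25 | 0.82 | 2.6 |
| Pooled, target | 61.9 | 1.24 | 3.9 |

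The ratio stays below 4 in every cell.

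**5. What this could mean for a fitted model.** An illustrative simulation assumed four true predictors (log odds ratio 0.5 per SD), independent normal variables, every term entered without shrinkage, and 100 runs per setting. The true AUC was about 0.75.

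| Setting | Terms | Apparent AUC | AUC in new data | Calibration slope |
|---|---|---|---|---|
| n = 275, 7.5% | 16 | 0.83 | 0.69 | 0.44 |
| n = 275, 7.5% | 40 | 0.92 | 0.62 | 0.13 |
| n = 550, 11.25% | 16 | 0.78 | 0.72 | 0.74 |
| n = 550, 11.25% | 40 | 0.83 | 0.68 | 0.44 |

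In the second row, 15 of the 100 runs gave no stable fit and were left out.

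**6. Other outcomes.** No complication rate is given, so events for that outcome cannot be counted. For six-month mortality, Section 1 cites 20% with and 3% without delirium. If those rates applied here, 275 patients would yield 275 × (0.075 × 0.20 + 0.925 × 0.03) = 11.8 deaths at target and 275 × (0.15 × 0.20 + 0.85 × 0.03) = 15.3 with no effect.

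**7. Timing.** No arithmetic applies. Section 2 admits postoperative factors, Section 6.2 collects factors that can follow delirium, and no section limits predictors to those that precede the outcome.

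**The case against.** The strongest reply is that Section 2 says the factors will be analysed, not that each one enters the model. Variable selection, shrinkage and validation are commonly left to a statistical analysis plan, which may exist. A reader might infer that the model is bound to overfit. The documents do not support that, because no modelling method is fixed; only a high risk is shown. This reply does not reach the timing problem: Section 2 states the predictor scope, and an analysis plan that followed it would inherit the fault.

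Other stronger readings also fail.

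- **That 21 is the event count for the risk model.** It applies to delirium only, in the prospective cohort only, and only if the target is met. The model also covers complications and mortality.
- **That frailty data exist only in the prospective cohort.** Section 3 names cognition, quality of life and depression as lacking. Section 8 plans to adjust the cohort comparison for medication, comorbidity, BMI, hearing or vision and home situation, and Section 6.2 calls the dependency score standard for all admissions. Some factors should therefore be in the historical records. The physiotherapy tests belong to the new pathway.
- **That every postoperative predictor is invalid.** For mortality after discharge, in-hospital complications, ICU stay and transfusion come before the outcome and can be legitimate predictors.
- **That the model's discrimination would be mostly noise.** A simulation with 50 independent pure-noise predictors screened at p < 0.05 gives a mean apparent AUC of about 0.71 with 21 events, against a true 0.50. That is a worst case. The protocol specifies no such screening, the laboratory items are plainly correlated, and Section 1 regards many of the factors as established.

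On the word *confirm* in Section 8.3, one can say that it means checking known associations, and Section 6.1 uses softer language. That is a fair reading of intent, but this many factors on this few events cannot confirm them.

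**Conclusion.** The point holds in two parts. First, the predictor scope in Section 2 is badly fixed: it lets factors that can follow delirium or in-hospital complications serve as predictors of them. This rests on the text alone. Second, delirium events (about 21, 41 or 62 by scenario) are too few for about 50 candidates, at 0.4 to 1.2 events each, so a model drawing on all factors is at high risk of overfitting.

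The second part rests on the protocol's 15% and 7.5% rates, full recruitment of 275, and my count of candidates with one term each. The conclusion is not sensitive to that count, since 16 terms still give only 1.3 to 3.9 events per term. The simulated AUCs show the size of the optimism under an unpenalised full model and do not predict what this trial will report. The issue concerns an additional objective; the primary comparison and its sample size are unaffected.

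**What to change.** - **Section 2:** state the time point at which risk is predicted, and restrict predictors to those known before it and before each outcome. For delirium and in-hospital complications, that means preoperative factors only. In-hospital factors should be allowed only in a separate model of mortality after discharge.
- **Delirium model:** use a short prespecified predictor set sized to the expected events, or a penalised (ridge or lasso) logistic model. Say which cohort it is fitted in. Report bootstrap optimism-corrected discrimination and calibration.
- **Section 8.3:** describe the frailty-factor associations as exploratory in place of *confirm*.

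The cost is slightly more analysis work and a model with less impressive apparent performance. No data collection changes.
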